## Abstract

**Introduction:**

Acutely hospitalised older patients often live with frailty and have an increased risk of impaired physical function. Previous studies suggest that exercise might mitigate the risk of physical impairment; however, further research is needed to compare the effect of different types of exercise interventions. In this paper, we report a protocol for a trial that aims to examine (1) if multicomponent exercise interventions (interventions that include both mobility and strengthening exercises) have effects on physical function compared with usual care in older adults and (2) if a comprehensive multicomponent exercise programme is more effective than a simple multicomponent exercise programme that only include walking and sit-to-stand exercises.

**Methods and analysis:**

This is a three-armed randomised controlled trial, with two intervention groups (comprehensive and simple exercise programme) and a control group receiving usual care. We will include 320 participants aged ≥75 years from geriatric medical departments of four hospitals in Stockholm, Sweden. Assessments will be conducted at hospital admission, discharge and 3 months thereafter concerning physical function (primary outcome), activities of daily living, health-related quality of life, sarcopenia and falls. The number of readmissions will be registered up to 1 year after discharge. Data will be analysed with linear mixed effects models, according to the intention-to-treat approach.

**Ethics and dissemination:**

Ethical approval for this trial has been granted by the Swedish Ethical Review Authority (approval number 2022-03032-01). Data collection will consider the information requirement, the requirement of consent, confidentiality obligations and the utilisation requirement. Trial findings will be disseminated through multiple channels, including scientific publications and conferences, and workshops with healthcare professionals and the public.

**Trial registration number:**

NCT05366075

STRENGTHS AND LIMITATIONS OF THIS STUDYIn order for the sample to be representative of older hospitalised patients, the participants will be consecutively recruited at several hospitals in Stockholm.Both exercise interventions use none or low technology exercise equipment that is already available in most hospital settings or can be purchased at a low price.The block design may result in selection bias in the trial; however, one advantage is that participants from both groups at the same department are avoided.

## Introduction

Hospitalisation due to acute medical illness is associated with several negative health consequences in older adults, even if the illness that caused the admission is successfully treated. Approximately, half of adults aged 65 years and older show a decline in physical function following acute hospitalisation.^1^ Many patients do not regain prehospital function, lose independence and have increased risk of reduced well-being, readmissions and death after discharge.^2 3^

Acutely hospitalised older patients often live with frailty and several concurrent diseases.^3^ Furthermore, acutely hospitalised older people spend most of their hospital stay in bed, even if they are able to walk independently.^4^ Such periods of physical inactivity, although short, may exacerbate the age-related loss of muscle mass, strength and physical function.^5 6^ It has been suggested that relatively small amounts of exercise might mitigate these deficits,^7 8^ emphasising the importance of identifying exercise interventions that are easy to use for older people during hospital stay.

A recent Cochrane review concluded that there is uncertainty regarding the effect of exercise interventions on functional outcomes for older medical inpatients during acute hospitalisation.^9^ Thus, it has been suggested that future research on this topic should focus on consistent reporting of participant characteristics, including baseline level of functional ability, as well as exercise dose and adherence to provide an insight into the reasons for the observed inconsistencies in findings.^9^

In a randomised controlled trial (RCT), Martínez-Velilla *et al* demonstrated that a comprehensive exercise programme, which consisted of several supervised exercises including progressive resistance, balance and walking exercise, provided significant health benefits over usual care in acutely hospitalised patients aged 75 years and older.^10^ Also, in another RCT, Ortiz-Alonso *et al* showed that a relatively simple multicomponent intervention solely consisting of walking and rising from a chair decreased the risk of dependence in activities of daily living (ADL) in acutely hospitalised patients older than 75 years.^11^ It is not known whether a simple exercise programme, such as the one by Ortiz-Alonso *et al* could yield similar health benefits as a more comprehensive intervention, such as the one by Martínez-Velilla *et al*. Considering the time constraints in acute care settings, a simple exercise programme may be more feasible if proven effective.

The main aims of the ‘preventing functional decline in acutely hospitalised older patients (PREV_FUNC)’ study are to (1) evaluate the effect of multicomponent exercise interventions (interventions that include both mobility and strengthening exercises) on physical function (primary outcome), ADL, health-related quality of life (HRQL), sarcopenia, falls, readmissions and mortality in comparison with usual care in acutely hospitalised people aged 75 years and older and (2) if a comprehensive multicomponent exercise programme that include several exercises is more effective than a simple multicomponent exercise programme that only include walking and sit-to-stand exercises. An initial pilot of the PREV_FUNC study suggested that the intervention was feasible, safe and acceptable to the participants (unpublished data). In this paper, we present a study protocol for the PREV_FUNC study.

## Methods and analysis

### Trial design

The PREV_FUNC study will be conducted in accordance with the Consolidated Standards of Reporting Trials.^12^ It is a three-armed single blind block randomised controlled multi-centre trial. Participants will be included consecutively from geriatric medical departments at four hospitals in Stockholm, Sweden. A flow chart of the participants is shown in figure 1. The patients will be included in the control group or one of the intervention groups in a time-dependent manner: participants will be recruited to each group during blocks of 2–3 weeks, which will be repeated until the end of the trial. The order of the groups will be randomised for each trial site (randomisation will be done by the responsible researchers). The block design has been chosen to avoid copresence of participants from intervention and control groups at the same department; that is, to prevent the exercises in the intervention groups from spreading to usual treatment and risk contaminating the control group.^11 12^ Eligible subjects will be invited to participate in the trial within 36 hours of admission and the baseline examination will be conducted directly after the inclusion. The trial has been registered at ClinicalTrials.gov, NCT05366075. This protocol is reported in accordance with the Standard Protocol Items: Recommendations for Interventional Trials.^13^

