### Inclusion and exclusion criteria

Inclusion criteria for participation are age 75 years and older, ability to stand up from a sitting position independently or with minimal personal help, and ability to communicate and collaborate with the research staff. People who cannot follow instructions will be excluded. Patients who by the responsible physician are assessed as not eligible to participate due to terminal illness or any major medical condition that contraindicates exercise will also be excluded. We will also exclude patients who live in nursing homes, or those who were previously included in the trial.

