#### Data collection

Physical function, ADL, HRQL, sarcopenia and falls will be assessed at baseline (hospital admission), discharge and 3 months after discharge. Research staff blinded to group allocation will conduct the tests and administer the questionnaires at the hospital (for the baseline and discharge evaluations) and at the home of the participants (for the 3-month evaluation). The 6-month and the 1-year evaluation will be conducted using patient records (for hospital readmissions and mortality) (table 2).

**Table 2 T2:** Time of assessment of the different variables in the trial

	Time point				
Assessment	Baseline (hospital admission)	After exercise/control period (discharge)	3 months after discharge	6 months after discharge	1 year after discharge
Primary outcome					
Physical function	X	X	X		
Secondary outcomes					
Activities of daily living	X	X	X		
Health-related quality of life	X	X	X		
Sarcopenia	X	X	X		
Falls after inclusion		X	X		
Hospital readmissions			X	X	X
Mortality			X	X	X
Additional data					
Frailty status	X				
Nutritional risk	X				
Nutritional supplementation	Continuously collected during the hospitalisation				
Falls in the previous year	X				
Demographic data	X				
Reason for hospital admission	X				
Comorbidities	X				
Length of hospital stay		X			
Discharge destination		X			

The primary outcome will be lower extremity physical function, assessed according to the Short Physical Performance Battery (SPPB).^15^ The SPPB has three components: standing balance, walking speed and the chair stand test for lower extremity strength. It has been validated in older adults living with frailty, is sensitive to change, and predicts a wide range of clinical outcomes.^16 17^

Secondary outcomes will be ADL (according to the Barthel Index),^18^ HRQL (according to the EuroQol-5 Dimension),^19^ presence of sarcopenia (defined by handgrip strength, calf circumference and arm circumference), according to the European Working Group’s revised criteria on Sarcopenia in Older People,^20^ and number of falls during follow-up (according to the logbooks at the hospital, and self-report at the 3-month follow-up). Data on vital status and number of readmissions up to 1 year after discharge will be collected using patient records.

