#### Data analysis

##### Power of the trial

We estimate that 264 participants should be included in the main RCT to enable detection of a clinically meaningful difference of one point in the main outcome (SPPB) at 3 months after discharge,^24^ when power is 0.80 and alpha is 0.05 (three group comparison). To take into account, approximately 20%of deaths or dropouts during 3 months, 320 participants should be included in the trial.

We will use the intention-to-treat approach. Between-group comparisons of change in the continuous variables from baseline to follow-up will be conducted using linear mixed effects models, with adjustments for baseline scores. To account for deaths and lost to follow-up, we will model the group comparisons through joint models, which will be performed by simultaneously estimating both a linear mixed model and a Cox’s proportional hazard regression model. Group differences in the number of readmissions will be examined using ordinal logistic regression models. Binary logistic regression models will be employed to examine between group differences in binary outcomes, and Cox’s proportional hazard regression model will be used for mortality data. Multiplicative interactions between sex and group allocation in relation to the outcomes will also be examined. Statistical analyses will be performed with Stata and R (version 16).

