This trial has some limitations. First, instead of a classic randomisation, we have chosen a block design, which may introduce selection bias in the trial. However, an advantage of the block design is that it avoids copresence of participants from both groups at the same department; and thus, prevents that the exercises in the intervention groups will spread to ordinary treatment and risk to contaminate the control group. If the exercises in the intervention groups would spread to the control group and produce unexpected clinical benefits, it could create a bias by disguising a possible genuine benefit of the interventions and reduce the effect size to a value that is not clinically significant. Therefore, it has been emphasised that researchers in clinical trials on rehabilitation topics should make sure that control groups do not include any of the active elements of the intervention such as physical exercise.^12^ Second, like usual care in the studies by Martínez-Velilla *et al* and Ortiz-Alonso *et al*,^10 11^ usual care at geriatric departments in Sweden include physiotherapy, and the patients may receive a limited amount of functional training when needed. This may introduce a bias in the trial since participants in the control group may also receive some physical exercise. However, a hospital stay is often accompanied by low levels of physical activity, which has been suggested to play a major role in causing the negative health consequences associated with hospitalisation.^4 14^ Third, the trial will include participants who are able to stand up from a sitting position, and to communicate and collaborate with the research team, which could limit the generalisability to those with relatively higher levels of functioning. However, the trial participants will be consecutively recruited at several hospitals, so that the sample will be representative of older hospitalised patients.

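### The arm is fixed by calendar block before eligibility, consent and baseline testing, and the stated primary model adjusts for the resulting selection risk only through the baseline score

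*Protocol article*

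**What the plan says.** Under Trial design, the Protocol article allocates by time: "participants will be recruited to each group during blocks of 2–3 weeks, which will be repeated until the end of the trial". The sequence is set per hospital: "The order of the groups will be randomised for each trial site (randomisation will be done by the responsible researchers"). No concealment step is described. Running one arm at a time is deliberate: "The block design has been chosen to avoid copresence of participants from intervention and control groups at the same department". Patients enter after the block's arm is set: "Eligible subjects will be invited to participate in the trial within 36 hours of admission", with the baseline examination straight after inclusion. Inclusion is consecutive.

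Under Inclusion and exclusion criteria, the responsible physician removes patients "assessed as not eligible to participate due to terminal illness or any major medical condition that contraindicates exercise will also be excluded".

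Under Data collection, "Research staff blinded to group allocation will conduct the tests and administer the questionnaires at the hospital" at baseline and discharge; the 3-month test, by the same blinded staff, is at the participant's home. Age, sex, comorbidities, Clinical Frailty Scale and nutritional risk are all recorded at baseline.

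The Discussion concedes that "instead of a classic randomisation, we have chosen a block design, which may introduce selection bias in the trial", and the strengths and limitations box says the same.

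Under Data analysis, continuous outcomes, including the primary, are compared with linear mixed models adjusted for baseline scores. A joint model handles death and loss to follow-up. A sex-by-group interaction is examined. For the rest, only the model type is named, for example: "Binary logistic regression models will be employed to examine between group differences in binary outcomes".

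**The concern.** In an individually randomised trial with concealment, nobody who decides on entry knows the next arm. Here the arm is common to everyone recruited at a site for weeks, and three decisions follow it: the physician's exclusion, the patient's consent and the baseline measurement. The exclusion about exercise has practical consequences in an exercise block and few in a usual-care block. Consent may also depend on whether the patient is being offered exercise.

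If either step works differently between blocks, the arms differ in case mix before treatment. The contrasts of exercise with usual care are then biased, and the contrast between the two programmes may be too. The Discussion answers its own concession with the avoidance of contamination. That justifies using blocks, but does not reduce selection bias. What remains is the analysis, and the article names only the baseline score as a covariate.

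A second, lesser exposure is testing at the hospital. With one arm running, a tester who sees or hears of the exercise sessions can infer the arm. Baseline SPPB is also the adjusting covariate, so a shift in its scoring would carry into the model.

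**Working it through.** **1. Order of events.** Block arm set → invitation → physician's eligibility judgement and consent → baseline test → treatment the same day or the next. Each entry decision comes after the arm is set. This holds whether the order of arms is drawn once per site or anew each cycle, because the current arm can be known throughout its block.

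**2. What each stated safeguard covers.**
- Consecutive inclusion: recruiter picking, but not physician exclusion or refusal.
- Baseline-score adjustment: imbalance carried by that score, but not imbalance in age, frailty, comorbidity or site beyond what the score reflects.
- Joint model: death and loss to follow-up, not selection at entry.
- Sex-by-group interaction: effect modification, not selection.

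**3. Scale for an illustration.** The article gives 264 evaluable participants, a 1-point difference, power 0.80 and alpha 0.05, but no SD, so 264 cannot be reproduced independently. Assuming equal arms (264/3 = 88) and a two-sided pairwise test, the implied SD is

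SD = √(88/2) / (1.960 + 0.842) = 6.633 / 2.802 = 2.37.

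Other readings of the three-group comparison imply 2.05 (Bonferroni for three comparisons) to 2.45 (global test). The point does not depend on this choice.

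**4. Residual selection bias (assumed inputs).** Let two arms differ by s SDs in a prognostic factor unrelated to baseline SPPB, with partial correlation r with 3-month SPPB. Then

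bias = r × s × SD; SE = 2.37 × √(2/88) = 0.357; bias/SE = r × s × √(88/2) = 6.633 × r × s.

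Type I error = 1 − Φ(1.96 − bias/SE) + Φ(−1.96 − bias/SE).

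| s | r | bias (points) | bias/SE | type I error |
|---|---|---|---|---|
| 0.1 | 0.2 | 0.05 | 0.13 | 5.2% |
| 0.3 | 0.3 | 0.21 | 0.60 | 9.2% |
| 0.5 | 0.5 | 0.59 | 1.66 | 38% |

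The ratio bias/SE contains no SD, so the error rates do not depend on the back-solved 2.37. If 2.37 is the SD before baseline adjustment and baseline correlates 0.7 with follow-up, the bias in points shrinks by √(1 − 0.49) = 0.714, so that 0.59 becomes 0.42. The SE shrinks equally and the error rates stay the same.

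**5. Scoring shift (assumed inputs).** If knowledge of the arm moved SPPB scoring by 0.1, 0.25 or 0.5 points, with the same SE of 0.357, type I error would be 5.9%, 10.8% or 28.8%. For the discharge test this also assumes that the SD and numbers are the same as at 3 months.

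**The case against.** The block design is a reasoned trade: contamination of usual care would dilute the effect, and the authors disclose the price. Inclusion is consecutive and the physician's criterion is the same for all arms. Patients excluded for poor function would mostly have low baseline SPPB, which the model adjusts for. Assessors are stated to be blinded, and covariate lists are often left to an analysis plan, which is not shown here.

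Much of this stands, and it rules out several stronger readings that a reader might infer:
- *That assessor blinding fails at the hospital.* The article says the testers are blinded and nothing in it contradicts this. It does not say that they are ward staff or see the sessions. The blinding is exposed, not shown to be broken.
- *That the sequence is known after the first cycle.* Over about 69.6 weeks of recruitment, a single draw with cycles of 6–9 weeks would leave 1 − 9/69.6 = 87% to 1 − 6/69.6 = 91% of the time predictable. But the article does not say whether the order is drawn once or every cycle, and the figure also needs every site to recruit throughout.
- *That selection favours exercise by 0.05–0.6 points.* That range is an extra excluded share times a deficit (0.05 × 1 to 0.20 × 3). Both inputs are assumptions, the result precedes the planned baseline adjustment, and stricter exclusion in exercise blocks is conjecture.
- *That the logistic models are unadjusted.* The article is silent on their covariates, which is not the same.

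What the objection does not remove is that the order of events leaves physician exclusion and refusal open to the arm, and that the only adjustment named for the primary outcome is the baseline score. An unseen analysis plan could add covariates, but it could not repair recruitment.

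**Conclusion.** The point holds as a weakness worth correcting. The arm is fixed, and can be known, before eligibility, consent and baseline testing. The concession of selection bias is matched by no remedy beyond baseline-score adjustment and consecutive inclusion, although stronger prognostic data are collected and the order is randomised by site.

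The size and direction of the residual bias cannot be derived from the documents. The illustrative 0.05–0.59 points, with type I error of 5.2%–38%, rests on assumed imbalances and correlations, equal arms of 88 and a normal approximation. Modest imbalance costs little, while large imbalance in a strong predictor could matter against a 1-point target. Blinding of the hospital tests is vulnerable. The 3-month home test, on which the trial is powered, is less exposed, since the assessor would have to infer the arm from the enrolment date or from the participant.

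**What to change.** 1. **Analysis.** Adjust the primary mixed and joint models for age, sex, Clinical Frailty Scale and site as well as the baseline score. Use the same covariates in the logistic, ordinal and Cox models, adding the outcome's baseline value only where one is measured (sarcopenia, for example). Mortality, readmissions and falls after inclusion have none. This uses data already collected, and reduces bias only through measured factors.
2. **Recruitment, for the remaining blocks.** Apply and record the same eligibility judgement in every block, including usual-care blocks. Report numbers screened, excluded and refused by arm. Complete consent and baseline SPPB before telling the patient the arm.
3. **Sequence.** State that the order is re-drawn in every cycle by someone not involved in recruitment. This reduces foreknowledge of later blocks; it does not hide the current arm.
4. **Assessment.** Where existing rosters allow, have the 3-month visit done by an assessor who did not work at that hospital in that block. Describe blinding of the hospital tests as vulnerable.

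The cost is a protocol update, small scheduling effort and slightly more analysis work. The block design and its protection against contamination are kept.

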**Figure 1 F1:**
[figure not shown]
Flow chart of the participants.

### Inclusion and exclusion criteria

Inclusion criteria for participation are age 75 years and older, ability to stand up from a sitting position independently or with minimal personal help, and ability to communicate and collaborate with the research staff. People who cannot follow instructions will be excluded. Patients who by the responsible physician are assessed as not eligible to participate due to terminal illness or any major medical condition that contraindicates exercise will also be excluded. We will also exclude patients who live in nursing homes, or those who were previously included in the trial.

